## Abstract

**Background:**

Falls are one of the most common accidents in older adults, often leading to injury, disability and quality-of-life declines. Foot core function contributes to postural stability in most static postures and dynamic activities. As efficient foot core training, the intrinsic-foot-muscle exercise has been proposed to improve postural control. However, the effects of the exercise on postural stability in the elderly remain unclear. Therefore, this study attempts to investigate the effect of 12-week intrinsic-foot-muscle exercise on postural stability in older adults with fall risk.

**Methods:**

We will conduct a prospective, single-blind randomised controlled trail on 120 older adults with fall risk. Participants will be randomly assigned to an intrinsic-foot-muscle exercise combining the lower extremity resistance training group (IFM group), an extrinsic-foot-muscle exercise combining the lower extremity resistance training group (EFM group) and a control group. The control group will perform lower extremity resistance training. The IFM and EFM groups will be given additional short-foot exercise or towel-curl exercise training, respectively. After the intervention, participants will be followed up for another 12 weeks with no active intervention. The outcome measures will include the postural stability measurements, self-reported postural stability, number of falls, intrinsic-foot-muscle strength and foot arch function. Furthermore, adverse events will be recorded and analysed. If any participant withdraws from the trial, an intention-to-treat analysis will be performed.

**Discussion:**

The trial is designed to investigate the efficacy of a 12-week intrinsic foot muscle training combined with the lower extremity resistance training on postural stability outcomes in elderly people with fall risk. The trial will also examine the comprehensive outcomes of postural stability during static standing and dynamic movements. The function of intrinsic foot muscle to support the arch will also be evaluated. Important features of this trial mainly include intervention setting, outcome measure selection and study duration. The results of this study will determine the effectiveness and provide scientific evidence to establish comprehensive fall prevention intervention.

**Trial registration:**

Chinese Clinical Trial Registry ChiCTR2000033623. Registered on 7 June 2020. http://www.chictr.org.cn/showproj.aspx?proj=54741

## Administrative information

Note: the numbers in curly brackets in this protocol refer to SPIRIT checklist item numbers. The order of the items has been modified to group similar items (see http://www.equator-network.org/reporting-guidelines/spirit-2013-statement-defining-standard-protocol-items-for-clinical-trials/).

## Introduction

### Background and rationale {6a}

Falls are the second leading cause of unintentional injury-related deaths among older adults, and falls can cause nonfatal injuries such as fracture and head injury [1, 2]. According to data of the Centres for Disease Control and Prevention, approximately one-third of people aged above 65 years in the USA reported falling in the preceding 12 months [3], and half of those fallers will fall again within the subsequent year [4]. Furthermore, falls substantially reduce the mobility and balance confidence of older people, imposing a significant medical and social burden. As estimated, the medical costs caused by fatal and nonfatal falls were approximately 50.0 billion USD for 1 year in the USA [5]. Similarly, in China, the aging and increasing fall-related injury in older adults is a growing public health concern. The medical cost of fall-related injury among older Chinese people ranged from 16 to 3812 USD per person per fall [6].

Falls, as a major public health issue, have attracted the attention of many researchers. For older individuals, multiple factors and complications are associated with falls, such as obesity, low lower-limb muscle quality and impaired postural control [7, 8]. Postural control is among the most common causes of falls in older adults, often leading to injury, disability and quality of life declines [9]. The functions of the vision, vestibular and musculoskeletal systems, as well as cognitive function, play an important role in human postural stability [10–12]. These physiological functions related to posture control would decline with age. Thus, effective intervention strategies to improve postural stability in the elderly are urgently needed.

The human foot is a highly complex structure, and it contributes to postural stability in most static postures and dynamic activities [13]. Owing to the technical constraints, previous researches of postural control focused on related physiological factors and postural adjustment strategies, while ignoring the role of the foot as an independent structure in postural control [7, 14]. In 2015, McKeon et al. [15] proposed a new paradigm of the foot core system that further refined the foot structure into active, passive and neural subsystems. As a direct interface between the body and the ground, the stability of the foot arch (passive subsystem) is a requisite to normal foot function and considered the core function of the foot [15]. Based on the coordination between controls of muscular activity (active subsystem) and the somatosensory afferent system (neural subsystem), the feet help to sense and interact with the environment [16].

Recently, with the development of foot and ankle biomechanics, several researchers have started to explore the role and mechanism of the foot core system in human postural stability [17, 18]. Previous studies suggested that the weakness of foot core stability is related to the decline of postural stability [19–21]. The functions of foot arch (passive subsystem) and foot sensory (neural subsystem) were associated with postural stability, and they declined with age [22, 23]. The intrinsic foot muscles and extrinsic foot muscles, which constitute the foot active subsystem, also play an active role in maintaining foot core stability [15]. Several studies have speculated that local dynamic support of the foot arch was provided from the intrinsic foot muscles [24].

Owing to a lack of understanding of intrinsic foot muscles, limited studies were designed to investigate the effect of the intrinsic muscles on postural control. Lee et al. [25] found that 8-week intrinsic foot training was more effective to improve the proprioception, dynamic balance and ankle stability index in individuals with ankle instability than traditional proprioceptive sensory training. In another study, after a 4-week programme of intrinsic foot training, a significant decrease was reported in medio-lateral displacement of the centre of pressure (COP) during the dynamic balance test [26] indicating the improvement in postural stability during dynamic activity. Studies have mainly focused on the postural control of healthy young adults and ankle instability, rather than individuals with balance disorders, such as the elderly. The effect of foot core stability training on the static postural control and the dynamic postural stability with the elderly must be investigated to develop a multifactorial effective management for the older adults with fall risk.

### Objectives {7}

Accordingly, the present study attempts to investigate the effects of intrinsic foot muscle intervention on the static postural control and the dynamic postural stability of older adults with fall risk. We will conduct a single-blind randomised controlled trial to investigate the efficacy of a 12-week intrinsic foot muscle training programme combined with the lower extremity resistance training on comprehensive outcomes in individuals with fall risk. The results of this study will determine the effectiveness and provide scientific evidence to establish comprehensive fall prevention intervention.

### Trial design {8}

This is a protocol for a parallel-group, single-blind randomised controlled trial (Fig. 1). It will follow the recommendation and suggestion of CONSORT 2010 (Consolidated Standards of Reporting Trials). The study will be carried out over a 12-week intervention (i.e., lower extremity resistance training), delivery and a 12-week follow-up.

**Fig. 1 Fig1:**
[figure not shown]
Flow diagram of study design. IFM group, intrinsic-foot-muscle exercise combined the lower extremity resistance training group; EFM group, extrinsic-foot-muscle exercise combined the lower extremity resistance training group; Control group, lower extremity resistance training group

Eligible participants will be randomised at a 1:1:1 ratio to enrol in one of the three groups. Three intervention programmes will be included in this study, namely, intrinsic-foot-muscle exercise combined with lower extremity resistance training (IFM), extrinsic-foot-muscle exercise combined lower extremity resistance training (EFM) and lower extremity resistance training programme (Fig. 1).

## Methods: participants, interventions and outcomes

### Study setting {9}

This study will be conducted at the Sport Medicine and Rehabilitation Centre, Shanghai University of Sport. In this study, the older participants with fall risk are defined by fall history and function test. The participants will be recruited from several community centres in Yangpu District, Shanghai, China. Before the initiation of the study, all participants will offer their basic information, including the medical history, history of falls and exercise habits. All personal data will be confidential and each subject will be provided informed consent before the inclusion in the study.

### Eligibility criteria {10}

Before baseline measurement, all participants will undergo screening to determine their current fall risk, including the self-report fall history for past 6 months and the Timed Up and Go (TUG) assessment [27].

#### Inclusion criteria

Adults older than 60 years oldAble to maintain the standing positionAble to walk alone, without others, prosthesis or mobility aidsNormal cognitive functionBe at moderate fall risk which is determined by one fall within the last 6 months and more than 10s of the TUG test [27]Availability: three times a week over 12 weeks

#### Exclusion criteria

Exclusion criteria include the following:
Participants diagnosed with diseases related to postural control, such as vestibular dysfunction, Alzheimer’s disease, Parkinson’s disease and motor neuron disordersHistory of lower limb trauma in the past yearSevere cardiopulmonary diseaseParticipants with medical contraindications for exerciseCurrently undertaking a structured exercise programme for postural control

### Additional consent provisions for collection and use of participant data and biological specimens {26b}

No biological samples will be obtained to be stored for use in this study. Additionally, the participants will be asked for permission of the continued use of their data in case of withdrawal from the trial or relevant studies in the future.

#### Concealment mechanism {16b}

The group randomisation will be separated into opaque envelopes kept by the main investigator. In addition, each participant will be represented by a separate number.

### Assignment of interventions: blinding

#### Who will be blinded {17a}

One physical therapist in charge of interventions will be blinded for baseline assessment. Furthermore, the researchers responsible for data collection and data analysis will be blinded for the random allocation. The participants will be instructed not to divulge the intervention accepted.

#### Procedure for unblinding if needed {17b}

Unblinding is permissible only when a serious adverse event or emergency rescue occurs.

### Interventions

#### Explanation for the choice of comparators {6b}

Although the optimal features of successful fall prevention exercise programmes are not yet clear, it has been recommended that the exercise aiming at improving lower extremity strength should be included in effective fall prevention programme. Therefore, the lower extremity resistance training was to be selected as a comparative intervention [28–30]. In this study, participants in IFM and EFM groups will extra receive two different types of foot muscle exercise, namely, short-foot exercise and towel-curl exercise. As a common foot muscle strengthening exercise, the towel-curl exercise primarily recruits extrinsic foot musculature, whereas the short-foot exercise has gained popularity involving isolate activation of the intrinsic foot musculature to reinforce the foot arch effectively [24, 26]. Different from the towel-curl exercise, during the short-foot exercise, the foot will be shortened by drawing the first metatarsophalangeal joint towards the calcaneus without toes curling [15].

#### Intervention description {11a}

The participants in each group will participate in respective intervention programme for 12 weeks. All training sessions will be done by a qualified physical therapist.

##### Intrinsic-foot-muscle exercise combined the lower extremity resistance training group (IFM)

Participants in the IFM group will be instructed to perform short-foot exercise according to the methods used in a previous study [25]. Under the supervision of the physical therapist, they will shorten their feet in the anterior-posterior direction without curling the toes, by actively drawing the head of the first metatarsal towards the heel. In short-foot exercise, the foot should be held for 5 s per repetition. The intensity of exercise will be divided into three levels (sitting position, double-leg stance and single-leg stance) with the overload increasing progressively. In general, for weeks 1–4, the IFM will be performed in a sitting position, subsequently performed in double-leg standing for weeks 5–8, and finally performed in single-leg standing for weeks 9–12.

Meanwhile, participants in the IFM group will undertake lower extremity resistance training. Thera-Band® resistance bands (The Hygenic Corporation, Akron. OH, USA) will be used during strength training. Likewise, training sessions will be supervised by a physical therapist to ensure correct training method and provide security. The programme of lower extremity resistance training includes extended leg raises, hip abduction, hip adduction, hip extension, knee extension, knee flexion, ankle plantarflexion and ankle dorsiflexion. The training will be progressed by increasing the strength of resistance bands to provide greater resistance.

The exercise regimen will comprise 3 blocks of 12 repetitions for IFM and resistance training, with a 2-min rest period between blocks. Each set will be performed bilaterally. Three sets will be performed 3 times per week for 12 weeks.

##### Extrinsic-foot-muscle exercise combined the lower extremity resistance training group (EFM)

The EFM group will undertake the towel-curl exercise and lower extremity resistance training group. During the towel-curl exercise, the physical therapist will place a towel on the floor and direct participants to place toes on the edge of the towel. Then, the participants will be instructed to drag the towel by flexing their toes. Similarly, the grip on the fabric will be held for 5 s per repetition [26]. Participants will perform the EFM exercise progressively under the position of sitting position, double-leg stance and single-leg stance like the IFM. The resistance training in the EFM group will be the same as the protocol in the IFM group.

The exercise regimen will be consistent in each training group. The participants will perform this training three times per week for 12 weeks.

##### Control group

The participants in the control group will perform the same lower extremity resistance training as the IFM and EFM groups. The training will also be supervised by the physical therapist. The entire intervention will be conducted under the protocol of the IFM and EFM groups and for the same duration.

#### Follow-up after intervention

The three groups will follow their respective training programmes for 12 weeks and will be followed up for another 12 weeks. After the intervention period, the participants will undergo a 12-week training period at home. During follow-up, they will be asked to maintain their previous lifestyle and continue interventions, respectively, and the physical therapist will provide guidance by telephone approximately once every 2 weeks. At week 24, these participants will return the laboratory and be reassessed.

### Outcomes {12}

This study will include assessments at the following time points: before intervention, after 12 weeks of intervention and after 12 weeks of further follow-up with home-based interventions. The total study period will be 6 months. All outcome measures assessments will be conducted by research assistants who are blinded to the subject assignment. Initially, all the participants will be submitted to fall risk test, comprised by the self-report fall history for the past 6 months and the TUG assessment. In addition, demographic data will be collected before the intervention. The data include subject characteristics (i.e., sex, age, height, weight, body mass index, degree of education and current drug treatment). Mentioned above tests will be conducted in a controlled environment by a trained researcher.

#### Primary outcome measures

##### Static postural stability

The NeuroCom Balance Manager System (Version 9.3, Copyright ©1989–2016 Natus Medical Incorporated) will be used to determine static postural stability. The balance platform is equipped with 18×60″ dual-force plate to measure the changes in COP of each participant. The COP will be collected when the participants stand on both feet with eyes open or eyes closed. We will calculate the same parameters as the postural stability test during standing: total length (TL), sway area (SA), maximum range of sway in the diction of AP, maximum range of sway in the diction of ML, mean velocity of COP sway and coefficient of variance of COP sway. The outcome data of static postural stability will be formatted as the difference at the points of baseline (week 0), post-intervention (week 12) and follow-up (week 24). The values will be shown as mean and standard deviation.

#### Secondary outcome measures

##### Stability during walking

In this study, the insole plantar pressure distribution measurement system (Novel Pedar, Germany) will be used to determine postural stability during the walking. Each insole contains 99 pressure sensors, which help to collect plantar pressure accurately and sensitively and to calculate the changes in COP in different tasks [31]. In advance of the testing, the pressure insole that fits the size of the participant’s shoe will be inserted into the left and right shoe and sampled at 100 Hz. Both insoles will be calibrated before data collection. The pressure measurement system will be presented to each participant and all procedures will be explained.

During the testing, the participants will be asked to walk 10 steps on a horizontal trail at their accustomed walking speed. Uniform shoes will be provided to prevent the effect of differences in shoes of the various participants. Three successful tests will be recorded for analysis without any unexpected movements in walking. To avoid the effects of walking start and braking, the data of the middle five steps of walking will be used for analysis. After we set the medial-lateral direction (ML) as *X*-axis and the anterior-posterior direction (AP) as *Y*-axis, the system will calculate the COP of each foot and it will be extracted to COP_L_ (*x*_1_, *y*_1_) and COP_R_ (*x*_2_, *y*_2_). Accordingly, the single COP for the whole body will be determined as ($$ \frac{x1+x2}{2} $$, $$ \frac{y1+y2}{2} $$). Then, we will calculate the following features from COP: TL, SA, maximum range of sway in the diction of AP, maximum range of sway in the diction of ML, mean velocity of COP sway and coefficient of variance of COP sway. The outcome data of stability during walking will be formatted as the difference at the points of baseline (week 0), post-intervention (week 12) and follow-up (week 24). The values will be shown as mean and standard deviation.

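### Walking stability: the unweighted midpoint of the two insole COPs is not the whole-body COP in gait, so the six secondary walking variables do not measure what they are named for

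*Protocol article*

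**What the plan says.** The protocol article, Secondary outcome measures, Stability during walking, measures gait with in-shoe pressure insoles. On the instrument it says "Each insole contains 99 pressure sensors", and that the insole "will be inserted into the left and right shoe and sampled at 100 Hz". On the task, "the participants will be asked to walk 10 steps on a horizontal trail at their accustomed walking speed", and "the data of the middle five steps of walking will be used for analysis".

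The axes are set as medial-lateral (ML) for X and anterior-posterior (AP) for Y. Then "the system will calculate the COP of each foot and it will be extracted to" a left pair (x1, y1) and a right pair (x2, y2). From these, "the single COP for the whole body will be determined as" ((x1+x2)/2, (y1+y2)/2). The formula has no force term.

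The outcome variables follow directly: "Then, we will calculate the following features from COP: TL, SA, maximum range of sway in the diction of AP", and the list continues with the ML range, mean velocity and coefficient of variance. That makes six variables, all computed from the midpoint.

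The primary outcome is measured differently. Under Static postural stability the article says "The balance platform is equipped with 18×60″ dual-force plate to measure the changes in COP of each participant". The SOT and LOS tests use the same balance system.

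**The concern.** A centre of pressure is the point where the total vertical force acts. With two feet on the ground it lies nearer to the foot that carries more load. A formula with fixed weights of one half ignores this. In quiet two-footed standing the loads may be close to equal and the midpoint may be tolerable. In walking the load moves from one foot to the other at every step, and for part of each step one foot carries everything.

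The formula is therefore wrong for most of the recording to which it is applied. All six variables inherit the wrong trajectory. What is at stake is the meaning of one secondary outcome: a change in it could not be read as a change in whole-body sway during gait.

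**Working it through.** The plan gives no figure to reproduce here, so the check compares the stated formula with the definition of the quantity it names.

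**Inputs from the protocol article (Stability during walking).** Positions (x1, y1) and (x2, y2); weights of 1/2 each; the middle five of ten walking steps; 100 Hz sampling; no restriction to double support.

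**Step 1, algebra.** Let F_L and F_R be the vertical forces under the two feet and s = F_L/(F_L + F_R).

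- Whole-body COP: C = (F_L·x1 + F_R·x2)/(F_L + F_R) = s·x1 + (1 − s)·x2, and the same for y.
- Stated midpoint: M = 0.5·x1 + 0.5·x2.
- Difference: C − M = (s − 0.5)(x1 − x2), so the error is |s − 0.5| × d, where d is the distance between the foot COPs.

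The error is zero only if s = 0.5 or d = 0.

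**Step 2, size as a share of d.** The load shares are assumptions; the documents give none.

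- 70/30: |0.7 − 0.5| = 0.20, so 20% of d.
- 90/10: |0.9 − 0.5| = 0.40, so 40% of d.
- Single support: |1.0 − 0.5| = 0.50, so half the distance to whatever position stands in for the unloaded foot. If none does, the formula is undefined, because that foot has no COP.

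**Step 3, size in centimetres, ML direction.** For an assumed ML separation of 0.10 to 0.20 m:

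| Load | Error |
|---|---|
| 50/50 | 0 |
| 60/40 | 1 to 2 cm |
| 75/25 | 2.5 to 5 cm |
| 90/10 | 4 to 8 cm |
| 100/0 | 5 to 10 cm |

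**Step 4, illustration over five steps.** This is a toy walk at 100 Hz in one common ground frame. Every gait value is assumed: ML separation 0.10 m, step length 0.55 m, step time 0.6 s, foot length 0.22 m, double support 20% to 40% of each step. The article does not say how an unloaded foot is coded, so three possibilities were tried.

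| Trajectory | ML range (m) | TL (m) | AP range (m) |
|---|---|---|---|
| Load-weighted | 0.10 | 2.81 | 2.75 |
| Midpoint, unloaded foot missing | 0.00 | 2.22 | 2.22 |
| Midpoint, unloaded foot coded (0,0) | 0.05 | 5.55 | 2.22 |
| Midpoint, last value held | 0.00 | 2.31 | 2.31 |

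In the second row the formula is undefined in 60% to 80% of frames. No midpoint version matches the load-weighted row: the ML transfer between the feet is halved or removed. The spread in TL comes from the assumed coding rules and is no estimate of what the trial would record.

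**Step 5, coordinate frame.** The article gives axis directions but does not describe how the two insoles are placed relative to each other. Steps 2 to 4 hold only in a common frame. If each pair is measured within its own shoe, |x1 − x2| is not a distance on the ground and these percentages do not apply. The average is then not a body-level position at all.

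**Step 6, what weighting alone would give.** In the toy walk the load-weighted AP range is 2.75 m = 5 × 0.55 m, which is the distance walked, and TL is only slightly longer at 2.81 m. Correct weighting alone would therefore not make TL or AP range a measure of stability.

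**The case against.** The strongest reply is that much of the processing is not visible. How swing-phase frames are treated, how an unloaded foot is exported and how the insoles are registered are details that an article may leave to a fuller protocol or laboratory procedure. This stands as far as it goes: nothing here should rest on a guess about the device's null value, and the toy walk is illustration only. It does not rescue the formula, which is printed in full with equal weights. A fuller document could add rules for swing frames, but it could not turn a stated equal weighting into a load weighting without contradicting the article.

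A second reply is that the same formula applies to all three arms at all three time points. This also stands. A reader might infer that the comparison of groups is biased; the documents do not show that. The defect is one of what is measured, possibly with added noise, and its effect on a group difference cannot be computed from the documents.

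A reader might also infer that a walking objective can no longer be answered. The Objectives section names static postural control and dynamic postural stability and states no separate walking objective. The closing paragraph of the Discussion lists walking as one of several conditions tested. The primary static outcome and the SOT and LOS do not use the formula.

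Finally, it is tempting to say that load weighting is mere post-processing because the sensors already record pressure. They can supply the force per foot, but the section records no foot positions, and the weighted formula needs both feet in one frame.

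**Conclusion.** The point holds for one secondary outcome. The midpoint is not the whole-body COP in gait except at instants of equal load, and all six walking variables depend on it. In a common frame the error is |s − 0.5| × d, from zero at equal load to half the distance between the feet in single support. This result is algebraic. The load shares, foot separations and gait values used to show its size are assumptions. Without a common frame the averaged point has no body-level meaning. As written, the variables do not measure what they are named for. This should be corrected before analysis.

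**What to change.** Replace the midpoint variables with COP features computed for each foot over its own stance phase, and say how left and right are combined for analysis. This uses the insole data already collected and asks nothing more of participants. The cost is that no single whole-body measure of walking stability remains, and the outcome should be relabelled accordingly.

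Use the force-weighted COP, (F_L·x1 + F_R·x2)/(F_L + F_R) and the same for y, only if foot positions are already recorded in one common frame. The forces can come from the summed insole pressures, and in single support the formula reduces to the loaded foot. In that case remove forward progression before computing TL and AP range, which otherwise largely reflect distance walked; mean velocity inherits the same problem if it is path length over time. If foot positions are not recorded, this option would need new data collection and should not be taken as a processing change.

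Either way, report the change of outcome definition as the article's section on communicating protocol amendments provides. The primary static outcome, the SOT and the LOS need no change on this account.
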